#### Hypotheses and exploratory analyses

##### Hypothesis 1

All participants will demonstrate improved suicide prevention knowledge from baseline after viewing the online teaching videos. We anticipate that this improvement will be maintained at the 6-month SP assessment. We do not anticipate a difference between the two conditions on knowledge measures. Repeated measures analysis of variance will be used to examine change in knowledge scores. Time will be examined as a within-subject factor (pre, post-videos, and follow up) with group entered as a between-subjects factor. Specifically, we hypothesize an overall time effect but no group or group by time interaction effects. Tryon’s inferential confidence intervals (ICI) will be used to assess for equivalency across treatment groups immediately post videos and immediately after the SP test case [31, 32]. In general, these inferential confidence intervals are adjusted so that “statistical difference” equates to two inferential confidence intervals that do not overlap (i.e., abutting at the upper or lower bounds). Establishing traditional 95% confidence intervals about each of two means, and concluding that the means differ *p* < .05 if the two intervals do not overlap, constitutes a greater burden of proof of statistical difference than would a corresponding t-test. To establish equivalence, however, a “Minimum Important Difference” (MID) must be established a-priori. By establishing MID’s, a context for determining statistical difference, equivalence, and indeterminacy is provided. Statistical differences exist when ICI’s do not overlap; statistical equivalence exists when the maximum probable mean difference estimate provided by the ICI (maximum upper bound of mean 1 and 2 minus the minimum lower bound of mean 1 and 2) is less than the MID and statistical difference does not exist. Indeterminacy exists when the means are neither statistically difference nor significantly equivalent. Following Treadwell and colleagues [33] a standardized small effect of .20 [34] will define the criterion for establishing a MID. As a form of sensitivity, a MID of .10 will also be examined.

##### Hypothesis 2

Participants in the experiment condition (simulation and feedback) will report greater self-efficacy in identifying and responding to patients at risk for suicide and greater intention to use the skills at 6 months compared to the control condition (those who only complete online teaching). We will use ANCOVA to assess SP training effects on satisfaction with the program, self-efficacy in identifying and managing patients who are at risk for suicide, and greater intention to use the skills at follow up. In all instances, the stratification variables of gender and training program group, as well as race/ethnicity/age and baseline status of the dependent variable (i.e., self-efficacy), will be included as covariates to aid in statistical power [35, 36]. If ceiling effects become an issue in any of these outcomes, tobit regression [37] will be used with the same covariates to assess for condition differences.

##### Exploratory analyses for Hypothesis 2

Moderation effects will be explored. The same ANCOVAs/tobit regressions described above will be conducted for each analysis but will also include interaction effects. Specifically, the cross-product of experimental condition by training group, baseline previous experience with suicidal patients, previous suicide prevention training, and baseline knowledge will be separately entered into each of the analyses. Procedures outlined by Aiken & West [38] will be used to minimize problems associated with multicollinearity. Multiplicative terms will be computed, first by centering each predictor variable and then forming the product term using the centered predictors of interest. Effect sizes, following Lipsey & Wilson [39], will also be examined as power to detect significant interactions will be limited [40]. The goals of these exploratory moderator questions are to better understand for whom the simulation training might be more effective (e.g., Do simulation training effects differ based on previous trainings/experiences with suicidal patients? Do simulation effects differ by training program group?).

##### Hypothesis 3

The primary hypothesis of the study is that participants in the experimental condition will demonstrate significantly better skills compared to the control group, as measured by reliable, observed ratings of behaviors in the SP assessment at 6 months. We will use ANCOVA to assess SP training effects at follow up on all participants’ skills. Skills will be measured by reliable observational ratings of several suicide specific and general interviewing skills. In all instances, gender, training program group, race/ethnicity, and age will be included as covariates to aid in statistical power [35, 36].

##### Exploratory analysis for hypothesis 3

We will examine statistical equivalence between the two SP modalities (face-to-face; telehealth). Similar to Hypothesis 1 (above), Tryon’s inferential confidence intervals will be used to assess for equivalency among face-to-face and telehealth modalities [31, 32]. Following Treadwell and colleagues [33], a standardized small effect of .20 [34] will define the criterion for establishing a MID. As a form of sensitivity, a MID of .10 will also be examined. As a second form of sensitivity, multilevel modeling will be used to decompose the variance associated with these observed training outcomes into variance attributed to the person as well as variance attributed to time (first SP interaction, second SP interaction) and variance attributed to modality. Since the order is randomized, we might expect more variance attributed to time (improving over time). Within these models, the learner (person) defines level 2 with the observed ratings being the dependent level one variables. Both time and modality will be entered as time varying covariates.

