Hypotheses are as follows: 1) All participants will gain suicide prevention knowledge from baseline after viewing online teaching and will maintain improvement at 6-month follow-up; 2) Participants in the experimental group will report greater satisfaction with the training, greater self-efficacy in identifying and responding to patients with suicidal thoughts and plans, and greater intention to use, as well as reported use of suicide prevention skills at 6-month follow-up; and 3) Participants in the experimental group will also be more skillful in responding to suicidal patients (demonstrated during the SP “test case” interview as measured by objective, observed ratings) compared to the control group at 6-month follow-up. Additionally, we will examine moderators of outcomes, differences between the two SP simulation modalities (i.e., face-to- face vs. telehealth modalities), and if there is improvement in skills observed over multiple SP interactions for the experimental group.

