### Participants

Participants are second year trainees from two education programs at the University of Rochester Medical Center: the nurse practitioner training program (NP) and medical residency programs, which included second year residents from pediatrics, the combined internal medicine-pediatrics program, and family medicine. These learner groups were chosen because most are preparing for careers in primary care. The training directors of the programs agreed to incorporate suicide prevention training into their curriculum for the duration of the grant and to support randomization of learners. As a result, all trainees receive the training according to their randomized condition. Trainees engage in a consent process (conducted by study personnel) for analysis of their data; those who do not consent for the study receive the training but their data are not analyzed. All trainee participants are fully informed that the SP interactions are part of their suicide prevention training. We collect non-identifiable demographic data at baseline for all trainees in order to compare those who enrolled in the study and those who did not. We plan to enroll 108 participants generally divided between residents and NPs.

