### Statistical analysis

#### Data processing

Data collection and storage is managed by REDCap, a secure software system supported by the institution. (Data management procedures are fully described in the study manual.) A baseline check of randomness will be conducted for each demographic and outcome variable collected. Because we are interested in establishing equivalence (as opposed to detecting differences), a more conservative alpha level will be applied (α = .20). Categorical variables will be analyzed using chi-square tests; continuous variable differences will be assessed using a general linear model approach (ANOVA). Any baseline difference will be controlled for statistically in all subsequent analyses. For analyses related to hypotheses, α = .05 and covariates will include stratification variables of gender and residency/NP training program, race/ethnicity, age, and the specific outcome baseline score as well as any other variables found to differ at baseline. Effect sizes (Hedge’s *g*) will also be examined for each of the study hypotheses.

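### Hypothesis 1 expects the knowledge gain to last to 6 months, but the only time result it names is an omnibus effect that cannot tell a kept gain from a lost one

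*Protocol article*

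**What the plan says.** The list of hypotheses in the Background of the protocol article says that all participants will gain knowledge and "will maintain improvement at 6-month follow-up". The Hypothesis 1 text under Hypotheses and exploratory analyses repeats this: "We anticipate that this improvement will be maintained at the 6-month SP assessment".

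The analysis, a repeated measures ANOVA of the knowledge scores, is set out in the same paragraph. Its factors are described in these terms: "Time will be examined as a within-subject factor (pre, post-videos, and follow up) with group entered as a between-subjects factor". The expected result is then given: "we hypothesize an overall time effect but no group or group by time interaction effects".

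The rest of the paragraph concerns Tryon's inferential confidence intervals, which "will be used to assess for equivalency across treatment groups immediately post videos and immediately after the SP test case", with a minimum important difference of .20 and a sensitivity value of .10. Data processing sets the error level ("For analyses related to hypotheses, α = .05") and says that Hedges' g will be examined for each hypothesis. Type 1 error protection applies a false discovery rate adjustment to the comparisons proposed. None of these sections names a contrast between time points for knowledge.

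**The concern.** The hypothesis has two parts: a rise after the videos, and its persistence at 6 months. The named result addresses neither part separately. An overall time effect on three levels says only that the three means are not all equal. It has no direction and does not say which time point differs.

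A rise followed by a complete return to baseline therefore produces the listed pattern as readily as a rise that is kept. At stake is the statement that 48 minutes of online teaching gives lasting knowledge. Read against the listed pattern alone, data in which nothing lasted would look like support.

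**Working it through.** **Plan's own figure.** The article gives no power or expected value for the Hypothesis 1 time test, so there is nothing to reproduce. The Power analyses section concerns a between-group effect with covariates and is not used here.

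**Inputs from the article**
- N = 108 (Participants: "We plan to enroll 108 participants generally divided between residents and NPs"), allocated 1:1 (Design), so 54 per group.
- Three time points, so the time effect has 2 numerator degrees of freedom.
- α = .05 (Data processing).
- Pre-to-post gain d = 0.90 to 1.35, cited for the original knowledge measure (Knowledge of suicide and suicide prevention). That measure is to be modified.

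**Assumptions not in the article**
- The gain is expressed in units of a common SD of 1.
- Compound symmetry, with within-person correlation ρ from 0 to 0.7.
- Lower gains of 0.30 and 0.50 SD, and N = 86 (about 20% loss), as sensitivity cases.

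**Step 1: squared deviations of the three means**
- Gain fully lost, means (0, d, 0): grand mean d/3. Sum = d²/9 + 4d²/9 + d²/9 = 2d²/3.
- Gain fully kept, means (0, d, d): grand mean 2d/3. Sum = 4d²/9 + d²/9 + d²/9 = 2d²/3.

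The two sums are equal for every d.

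**Step 2: power of the time effect.** The noncentrality is λ = N × (2d²/3)/(1 − ρ), with 2 and 2(N − 2) = 212 degrees of freedom. It is the same for both patterns.

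| d | ρ | λ | Power, gain lost | Power, gain kept |
|---|---|---|---|---|
| 0.90 | 0 | 108 × 0.54 = 58.32 | > .999 | > .999 |
| 0.90 | 0.7 | 58.32/0.3 = 194.4 | > .999 | > .999 |
| 0.30 | 0 | 108 × 0.06 = 6.48 | .613 | .613 |
| 0.30 | 0.5 | 6.48/0.5 = 12.96 | .903 | .903 |
| 0.30 | 0.7 | 6.48/0.3 = 21.6 | .990 | .990 |

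For d = 0.50, power is .973 to above .999 for both patterns. For d = 0.90 and N = 86 it is still above .999 for both.

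**Step 3: the full listed pattern.** This was simulated with 4,000 trials per row, N = 108, ρ = 0.5, a 0.90 SD gain, and no true difference between arms. The pattern column counts trials with time significant and both group and interaction not significant.

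| Follow-up scenario | Listed pattern | Follow-up significantly above pre | Follow-up significantly below post-videos |
|---|---|---|---|
| Gain lost | 90.0% | 2.8% | 100% |
| Half kept | 90.5% | 99.8% | 99.5% |
| Gain kept | 90.0% | 100% | 2.5% |
| 0.3 SD below baseline | 90.1% | 0% | 100% |

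The listed pattern is about equally frequent in every row. Its level near 90% is what remains after two true-null tests at 5% (0.95 × 0.95 = 0.9025). The two contrasts separate the scenarios.

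**Step 4: how far follow-up minus pre goes.** At ρ = 0.5 its standard error is √(2 × 0.5/108) = 0.096 SD. If only 0.27 of a 0.90 SD gain is kept (70% lost), then 0.27/0.096 = 2.81, and the contrast is significant with probability of about Φ(2.81 − 1.96) = .80. This contrast shows that some gain is retained, not that the gain is maintained.

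**The case against.** The strongest reply is that the article states no decision rule. The sentence lists the ANOVA terms that the authors expect to see. It does not say that a significant time effect confirms Hypothesis 1, and nothing rules out comparing the three means afterwards. Such follow-up comparisons are commonly left to an analysis plan, which is not shown. Effect sizes are promised for each hypothesis, so the omnibus p-value is not the only output, and anyone who saw the follow-up mean back at baseline would be unlikely to claim maintenance.

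Much of this stands. A reader might infer that the plan would declare maintenance from the time effect alone, or that the time effect is bound to be significant when the gain is lost. The documents support neither reading. No confirmation rule is written, and significance is near certain only at gains such as those cited for the original measure. At 0.30 SD the probability is about 61% to 99%, depending on an assumed correlation.

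What remains is a mismatch, not an omission. The article states what it expects of the analysis, and that result carries no information on one of the two things hypothesised. The other provisions do not close the gap:
- Tryon's intervals compare arms, and two arms that both lose the gain would still be alike.
- The effect-size and false discovery rate provisions name no time contrast.
- The growth curve analysis concerns observed skills in the experimental arm, not knowledge.

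**Conclusion.** The concern holds in this limited form: the only time-related result named for Hypothesis 1 cannot support its claim that the gain is maintained. The omnibus test has equal power under full loss and full retention: above .999 for both at 0.90 SD, and about .61 to .99 for both at 0.30 SD, with N = 108.

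The exact equality rests on compound symmetry. With another covariance pattern the two powers could differ somewhat, but the test would still have no direction. The 0.90 SD figure belongs to the measure before modification, while the equality of the two sums in step 1 does not depend on the size of the gain.

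Severity is minor to moderate. Hypothesis 1 is not primary, the maintenance claim is a pooled change over time and not the randomised comparison, and neither the sample size nor Hypothesis 3 depends on it.

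**What to change.** In the Hypothesis 1 text, replace the reference to an overall time effect with planned contrasts from the same repeated measures model:

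1. Post-videos minus pre greater than 0, for improvement.
2. Follow-up minus pre greater than 0, for some gain retained.
3. Follow-up minus post-videos, reported with its confidence interval. Describe the gain as maintained only if the lower limit excludes a loss larger than a margin stated in advance. Otherwise claim only that knowledge remains above baseline, provided contrast 2 supports it.

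The expectation of no group or interaction effect and the between-arm intervals can stay as they are.

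The cost is a few sentences, with the same data and model, and a somewhat stricter criterion for a non-primary hypothesis. The margin should be chosen with the precision in mind. At ρ = 0.5 the 95% half-width for contrast 3 is 1.96 × 0.096 = 0.19 SD. If there were truly no loss, a margin of 0.20 SD (the size that the article already uses between arms) would be met with probability of about Φ(0.20/0.0962 − 1.96) = .55. At ρ = 0 the standard error is √(2/108) = 0.136 and the probability about .31. At ρ = 0.7 they are √(0.6/108) = 0.0745 and about .77. Missing the margin limits only the wording of the claim.

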### Design

The study is a randomized controlled trial with an experimental group and a control group allocated with a 1:1 randomization ratio. All trainees are randomized to control and experimental learning groups using Wei’s urn randomization [23] which provides overall balance at the end of accrual but also gives good, often near-perfect, balance within many strata [24, 25]. Randomization strata include medical learner groups (i.e., medical residents, pediatric residents, and nurse practitioners) and gender. After all baseline measures are completed, participants are randomized to experimental condition by the project statistician, who remains blinded to study condition.

Participants in both groups complete a 48-min, 6-module, online video-based training on suicide prevention (Commitment to Living for Primary Care; CTL-PC). Upon completion of the online teaching program, participants in the experimental group engage in two standardized patient practice interactions over the course of 4 to 6 months. One practice interaction takes place in-person and the other uses a telehealth model. The order is randomized. Then, approximately 6 to 8 months (depending on schedules, see below) after video-based learning, both control and experimental groups engage in an in-person “test case” standardized patient interaction.

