##### Power analyses

Optimal Design software [43] was used to assess statistical power. As previously stated, covariates will be included in all models to help improve power to detect a treatment effect [35, 36]. Power will be computed on a modest effect size estimate of .30. With a minimum final sample size of 108 participants and explaining 40% of the variance in the outcome, we have .51 power to detect an effect size of .30. However, power increases to .80 if 50% of the outcome variance is explained by covariates. If 60% of the outcome variance is explained via covariates, we have greater than .80 power to detect an effect size of .20. We believe that an effect size of .30 is attainable and we also expect that baseline values of the dependent variable of interest as well as other baseline variables are likely to account for 50% of the variance in the dependent variable. While we recognize that power will be more limited for the exploratory questions addressed (and will supplement all analyses with the use of effect sizes), we do feel that the knowledge gleaned will provide useful information with regard to dissemination of the simulation training — addressing whether implementation via telehealth is statistically equivalent to in-person implementation as well as providing preliminary knowledge about the amount and predictors of change over time.

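### With 108 trainees the equivalence rule for knowledge between arms cannot be met at a margin of .20 or .10 SD, and for telehealth versus face-to-face it can be met only if the two sessions are very highly correlated

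*Protocol article*

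**What the plan says.** Under Hypothesis 1 the protocol article expects no difference in knowledge between the arms. It plans to test this with Tryon's inferential confidence intervals at two times: just after the videos and just after the standardized patient (SP) test case. Equivalence requires the larger upper bound minus the smaller lower bound to be below the MID, with no statistical difference. Anything that is neither different nor equivalent is indeterminate. On the margin, "a standardized small effect of .20 [34] will define the criterion for establishing a MID", and "As a form of sensitivity, a MID of .10 will also be examined".

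The exploratory analysis for Hypothesis 3 uses the same method and margins for the two practice sessions: "Tryon’s inferential confidence intervals will be used to assess for equivalency among face-to-face and telehealth modalities".

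The sample is fixed elsewhere. The Participants section says "We plan to enroll 108 participants generally divided between residents and NPs", and the Design section says "allocated with a 1:1 randomization ratio". Data processing sets the error level: "For analyses related to hypotheses, α = .05 and covariates will include stratification variables of gender and residency/NP training program". The Power analyses section gives power only for detecting differences. It concedes that power for exploratory questions is limited, yet lists among the expected gains "addressing whether implementation via telehealth is statistically equivalent to in-person implementation".

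**The concern.** An equivalence rule is useful only if the data could satisfy it. This rule compares a fixed margin with a span that contains the full sampling error of the difference, so the sample size sets a floor under the span. If the floor lies above the margin, the verdict of equivalence is ruled out before any data are collected.

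The expectation of no group difference in knowledge would then rest on a non-significant group or interaction effect, which is not evidence of equivalence. An indeterminate result could also be read as a finding about the training when it was fixed by the design. The same question arises for telehealth, where the article tells readers to expect an answer on equivalence.

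**Working it through.** **Inputs.** N = 108 at 1:1, so 54 per arm (Design, Participants, Power analyses). Alpha = .05 for hypothesis analyses, taken as two-sided (Data processing). MID = .20 and .10 (Hypothesis 1; exploratory analysis for Hypothesis 3). R-squared = .40, .50 and .60 are the values in Power analyses, which expects .50. The modality comparison is within person in the experimental arm, about 54 pairs (Procedures). The within-person correlation rho is not given, so it is varied. Margins are read in units of the unadjusted outcome SD.

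**The plan's own figure.** The article states "With a minimum final sample size of 108 participants and explaining 40% of the variance in the outcome, we have .51 power" for an effect of .30. With 54 per arm and residual SD sqrt(1 − .40), two-sided power is .52 by the normal approximation and .514 by the noncentral t. The .51 reproduces, which confirms the reading of N, alpha and R-squared. Other power figures in that section are not used here.

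**The floor.** Inferential confidence intervals are scaled so that just touching corresponds to p = .05. Their half-widths therefore add up to t × SE(difference). Hence:

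span ≥ |observed difference| + t × SE(difference) ≥ t × SE(difference).

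**Between arms.** SE = sqrt(2(1 − R²)/54), and t on 106 df is 1.983.

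| R² | SE | Smallest span, 95% | Smallest span, 90% |
|---|---|---|---|
| 0 | .1925 | .38 | .32 |
| .40 | .1491 | .30 | .25 |
| .50 | .1361 | .27 | .23 |
| .60 | .1217 | .24 | .202 |

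Every entry exceeds .20. In 200,000 simulated trials with identical groups and no adjustment, equivalence was never declared and the smallest span was .38 SD. Solving t × SE = MID at 95% gives R² = 1 − (MID/1.983)² × 54/2, which is .725 for .20 and .931 for .10. To bring the floor below .20 at all, the sample would need about 193 per arm unadjusted, from 2 × (1.96/.20)² = 192.1, or about 97 per arm at R² = .50.

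**Telehealth versus face-to-face.** Allowing for the pairing, which favours the plan, SE = sqrt(2(1 − rho)/54), and t on 53 df is 2.006. The smallest span is .39, .27 and .21 SD at rho = 0, .5 and .7. It falls below .20 only when rho exceeds .732, and below .10 only when rho exceeds .933. With a true difference of 0, P(equivalence) = 2Φ((MID − t × SE)/SE) − 1 where the floor is below the MID, and 0 otherwise:

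| rho | Smallest span | P at .20 | P at .10 |
|---|---|---|---|
| .70 | .211 | 0 | 0 |
| .75 | .193 | .06 | 0 |
| .80 | .173 | .25 | 0 |
| .85 | .149 | .50 | 0 |
| .90 | .122 | .80 | 0 |

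**Margins this sample could meet between arms** (same formula, true difference 0). Unadjusted: (.50 − .382)/.1925 gives .46 at a margin of .50, and .74 at .60. At R² = .50: (.40 − .270)/.1361 gives about .66 at a margin of .40, and .91 at .50.

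**The case against.** The strongest reply concerns reach. A reader might infer that Hypothesis 1 as a whole cannot be supported. The documents do not say that. At the end of the Background, Hypothesis 1 is stated as a gain in knowledge that is maintained at six months. The time effect in the repeated measures analysis tests this, and the margin does not touch it. Only the added expectation of no group difference depends on the equivalence rule. The primary hypothesis is superiority on observed skills, and neither equivalence test bears on it. An unreachable rule also errs only towards indeterminate, an outcome the plan provides for, so it cannot produce a false claim of equivalence. All of this stands and limits the weight of the point.

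A reader might also infer that modality equivalence could almost never be declared. That needs a correlation the document does not supply. Different scenarios at least a month apart, with feedback after the first, make a correlation of .85 or .90 seem unlikely, but that is a judgement. At .90 the rule would succeed 80% of the time at the .20 margin. The article also admits limited power for exploratory questions and promises effect sizes. That admission largely covers the modality comparison but not the Hypothesis 1 test, and it sits beside the telehealth equivalence claim.

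Covariate adjustment does not rescue the between-arm test, because no R-squared the article considers is high enough. Nor do 90% limits. The looser alpha of .20 in Data processing is for the baseline check only. None of this is detail left to a fuller document: the rule, margins, alpha and sample size are all stated and do not fit together.

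**Conclusion.** The point holds and should be fixed, although it does not threaten the primary analysis. Between arms, the rule can return only a difference or an indeterminate result at either margin. The smallest span is .38 SD unadjusted and .24 SD at the highest R-squared the article considers. This assumes 54 analysed per arm and 95% limits, and it would change only if covariates explained more than about 73% of the variance (93% for the .10 margin). The article expects some missing data, and any loss widens the span.

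For telehealth versus face-to-face the conclusion is conditional: equivalence at .20 is impossible up to a correlation of about .73 and becomes progressively attainable above it. At .10 the threshold is about .93.

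**What to change.** - **Hypothesis 1.** Replace the declare-equivalence rule at .20 and .10 with the covariate-adjusted between-arm difference in knowledge at each time point, its 95% confidence interval, and a statement of which standardised differences the interval excludes. At best that is differences beyond about .38 SD unadjusted, or about .27 SD at R-squared .50.
- **Exploratory analysis for Hypothesis 3.** Do the same for modality, using within-person differences. The multilevel model already planned as a sensitivity analysis includes session number and modality and can supply the interval.
- **Power analyses.** Restate the telehealth sentence as estimation of the modality difference, not a test of equivalence.
- **If a margin is kept.** Justify it on substantive grounds and state its probability of success with the assumed R-squared or rho. The wider margins in the working show what the sample could support and are not recommendations.

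The cost is wording in three places, with no change to data collection. The sponsor gives up an equivalence claim that, between arms, the design cannot deliver.

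### The second sensitivity analysis for face-to-face/telehealth equivalence is described only as shares of variance, which cannot be read against the plan's minimum important difference

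*Protocol article*

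**What the plan says.** The protocol article, under the exploratory analysis for Hypothesis 3, sets out three layers.

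- Main analysis: "Tryon’s inferential confidence intervals will be used to assess for equivalency among face-to-face and telehealth modalities", where "a standardized small effect of .20 [34] will define the criterion for establishing a MID".
- First sensitivity analysis: "As a form of sensitivity, a MID of .10 will also be examined".
- Second sensitivity analysis: "multilevel modeling will be used to decompose the variance associated with these observed training outcomes into variance attributed to the person", with further components for time (first or second practice session) and for modality. The only expectation given is "Since the order is randomized, we might expect more variance attributed to time (improving over time"). The model is specified with the learner at level 2, and "Both time and modality will be entered as time varying covariates".

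The decision rule for equivalence stands under Hypothesis 1, and the modality comparison is said to follow the same approach. A MID must be fixed in advance. Equivalence holds only if the largest probable mean difference is below the MID and no statistical difference exists. Anything that is neither different nor equivalent is indeterminate.

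The power section adds that the authors "will supplement all analyses with the use of effect sizes" and says the modality question should inform dissemination of the training.

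**The concern.** A sensitivity analysis should answer the same question as the main analysis under altered assumptions, so that the two can agree or disagree. By the plan's own rule, the question is whether a bounded mean difference lies below .20 SD. The second sensitivity analysis is described by a different quantity, the proportion of variance attached to modality. It has no margin, no bound and no link to the MID.

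A share also grows with the square of the difference, so differences well above the MID still give small percentages. Setting the modality share beside the time share does not help, because the time share reflects how fast trainees learn. A report that modality explains little variance, and time more, could be taken as backing for telehealth equivalence when it says nothing about the margin.

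**Working it through.** The document states no variance share, precision or power for the modality comparison, so there is no figure of its own to reproduce.

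**Inputs from the protocol.** MIDs of .20 and .10 (exploratory analysis for Hypothesis 3). Total sample 108 (power section) with 1:1 allocation (Design), so about 108/2 = 54 experimental participants. Each has one face-to-face and one telehealth practice session in randomized order. Alpha is .05, taken here as two-sided.

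**Assumptions.** SD of 1 within each session-by-modality cell; within-person correlation ρ of .3, .5 or .7; session-to-session gain g varied, since none is given.

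**Step 1: share of total variance for modality.** For a balanced two-level factor with difference d and no gain, the share is (d²/4)/(1 + d²/4).

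| d (SD) | d²/4 | share of total |
|---|---|---|
| .10 | .0025 | 0.25% |
| .20 (MID) | .0100 | 1.0% |
| .30 | .0225 | 2.2% |
| .50 | .0625 | 5.9% |

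The document does not fix the denominator. Against within-person variance, the share is (d²/4)/(1 − ρ + d²/4). At d = .50 this is 8%, 11% or 17% for ρ = .3, .5 or .7. At d = .20 it is 1.4%, 2.0% or 3.2%. The same difference therefore yields quite different percentages, and none of them is a statement about .20 SD.

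**Step 2: time share against modality share.** With both effects the shares are (g²/4)/T and (d²/4)/T, where T = 1 + d²/4 + g²/4. For d = .50:

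| g (SD) | modality | time |
|---|---|---|
| .3 | 5.8% | 2.1% |
| .5 | 5.6% | 5.6% |
| .6 | 5.4% | 7.8% |
| .8 | 5.1% | 13.1% |
| 1.0 | 4.8% | 19.0% |

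The modality difference is 2.5 times the MID in every row (.50/.20), yet the ordering turns on g alone. In simulated trials with n = 54 and ρ from .3 to .7, time exceeded modality in about 91–98% of runs at g = .8, about 50% at g = .5 and 9–19% at g = .3. The ordering can mislead the other way too. With d = .15 (inside the MID) and g = .10, modality has .0056/1.0081 = 0.56% and time .0025/1.0081 = 0.25%.

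**Step 3: what the same model gives on the right scale.** Modality is already a covariate, so the fit yields a session-adjusted coefficient with SE = √(2(1 − ρ)/54). The t quantile on 52 df is 2.007.

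| ρ | SE | 95% half-width | 95% CI at observed .50 | power at true .50 |
|---|---|---|---|---|
| .3 | .161 | .32 | .18 to .82 | .86 |
| .5 | .136 | .27 | .23 to .77 | .95 |
| .7 | .105 | .21 | .29 to .71 | .996 |

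Every interval at .50 extends above .20, so equivalence would not be declared.

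**Step 4: limit of the repaired analysis.** Even at an observed difference of zero, the upper bound is below .20 only if the half-width is below .20. That requires 2(1 − ρ)/54 < (.20/2.007)² = .00993, so 1 − ρ < .268, or ρ above about .73. For the .10 MID it requires 1 − ρ < 27 × (.10/2.007)² = .067, or ρ above about .93.

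**The case against.** The strongest reply has four parts.

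1. The plan never says that a larger share for time counts as evidence of equivalence. The sentence about time is a tentative expectation about learning. This stands: a reader might infer such a rule, but none is stated.
2. The verdict on equivalence comes from the inferential confidence intervals and the MID, which would not declare equivalence at an observed .50 SD. This also stands, and the main analysis is not undermined.
3. The model produces a modality coefficient, effect sizes are promised for all analyses, and the article does not say the coefficient will be set aside. This stands in part. It would be wrong to say that the plan discards the coefficient, which would usually flag a .50 SD difference. But a general promise of effect sizes supplies no bound to compare with the MID, and the output named for this analysis is still the variance decomposition.
4. Reporting detail for an exploratory sensitivity analysis belongs in a fuller analysis plan. That would answer a complaint about a missing margin. It does not answer this one, because the article does state the output, and that output does not suit its stated purpose.

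A reader might also infer that the analysis would look reassuring whenever trainees improve. Step 2 shows otherwise: with a gain of .3 SD and a modality difference of .50 SD, time exceeds modality in only 9–19% of trials.

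**Conclusion.** The point holds in limited form. The second sensitivity analysis, as described, cannot confirm or contradict equivalence at .20 or .10 SD, because a variance share is quadratic in the difference and carries no bound. A difference at the MID is about 1% of total variance, and one 2.5 times as large is about 6%. Its rank against time depends on an unknown gain. It could be misread as support for equivalence; the document does not show that it would be.

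The share figures assume balanced modalities and unit within-cell SD. The precision figures also assume 54 participants with both sessions and a within-person correlation of .3 to .7. The .50 SD difference and the gains are illustrations, not figures from the protocol. The matter is minor: it concerns an exploratory question, and neither the primary comparison nor the main equivalence test depends on it.

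**What to change.** Keep the multilevel model and change its named output. Report the modality coefficient (face-to-face minus telehealth, adjusted for session) with its 95% confidence interval in SD units. Read it against the .20 and .10 MIDs under the different/equivalent/indeterminate rule already set out for Hypothesis 1. Label the person, time and modality shares as descriptive, and state the denominator used.

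The cost is a sentence or two in the analysis plan; no new data or model is needed. The downside is candour about precision. With a half-width of about .21 to .32 SD, the result will nearly always be indeterminate unless a difference is shown, and the plan should state this in advance.
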